#### Control schools

College students of nutrition will deliver two educational workshops for parents once the intervention and assessment is completed (one HE and one on PA). These workshops will be crafted with the additional goal of showing appreciation to the parents for their participation in the assessment (thus enhancing the study’s retention rate), and to improve the school staffs’ interest and commitment in its support of the periodic assessment.

### Data collection

Due to logistic reasons the participating schools will be join the program in a series of steps. The first assessment interview (baseline) will take place sometime between June and October 2015. The second assessment interview (at the end of the intervention) will take place 12 months later. In the few cases where the adult participant of the dyad is different from the mother (typically a father), he will not be included in the anthropometric assessment.

Data will be be collected via questionnaires and objective measurements. The child is only subject to the latter; only the mother will respond to the former. The questionnaires will be administered in face-to-face interviews with the participating mother. After ending the baseline interview, mothers will receive instructions regarding the use of the accelerometer with a diary to be filled out by the mother during the 7 consecutive days of use. Eight days later, a research assistant will retrieve the child’s accelerometer at school.

### Measures

Detailed and specific measures for each dyad member and assessment time are shown in Table 2.

**Table 2 Tab2:** Assessment methods, timeline, and outcomes

Measurement	Source	Measure or instrument	Outcomes
Anthropometry	Child	Weight (kg), height (cm), waist circumference (cm)	BMI Z-score, overweight, obesity and central obesity.
	Mother (or father or guardian)	Weight (kg), height (cm), waist circumference (cm)	
Blood Pressure	Child	Blood pressure (mm Hg)	Classification of blood pressure (high, normal or low).
	Mother (or father or guardian)	Blood pressure (mm Hg)	
Physical Activity (PA) and Sedentary Behaviour	Child	Accelerometer	Accelerometer: Daily steps, minutes of moderate to vigorous PA (min/day), weekly METs (week days and week-end days) and sedentary time.
	Mother (or father or guardian)	Global Physical Activity Questionnaire (GPAQ - WHO)	GPAQ: sedentary behaviour and PA at work, during leisure, and for transport (min/day).
Dietary Intake	Child	24-h Recall using the Multiple Pass Method (completed by parent/guardian)	Daily caloric intake (Kcal/day), breakfast quality (mg calcium/day), portions of fruits and vegetables, volume of water (ml/day), and percentage of calories from saturated fats and of grams of added sugar coming from snacks.
	Mother (or father or guardian)	24-h Recall using the Multiple Pass Method	
Socio-Economic Status	Mother (or father or guardian)	Modified and adapted version of SAIMO Socio-Economic Level Survey	Classification of social and economic status (low, middle or high).
Home and Neighbourhood Environment	Mother (or father or guardian)	Modified and adapted version of ISCOLE Neighbourhood & Home Environment Questionnaire	Neighbourhood social capital, home social environment, home and neighbourhood food environments, home and neighbourhood PA environment and neighbourhood facilities environment.
School Environment	School Principal (or Vice- Principal, or School Secretary)	Modified and adapted version of ISCOLE School Environment Questionnaire	School facilities, healthy eating and PA policies, extracurricular activities, frequency of physical education and breaks, promotion of active transportation and the availability of healthy and unhealthy foods.

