### Anthropometric measures

#### Child and mother

Anthropometric measures will be taken at baseline and 12 months according to standardized procedures. Weight will be measured to the nearest 0.1 kg using a portable digital scale (SECA AURA 807) wearing light clothes. Height will be measured to the nearest 0.1 cm and with a portable stadiometer (SECA 206. Hamburg, Germany), with participant fully erect, without shoes, feet together, head in the Frankfort Plane and at the end of a deep inhalation. Waist circumference will be measured to the nearest 0.1 cm at the end of gentle expiration with a non-elastic anthropometric tape held midway between the lower rib margin and the iliac crest (Sanny, Berasil), utilizing the hands crossed technique in mid-waist for adults (WHO) and in minimal waist for children [36]. Central obesity in adults will be defined for each sex according to WHO recommendations [37] (females: > 88 cm; males: >102 cm). In children, central obesity will be defined using Taylor et al.’s cut-offs. [36]. The BMI Z-score will be calculated using the WHO reference growth charts for children [38] and for adults.

Each measure will be repeated, and the average will be used for analysis.

Blood pressure will be assessed at baseline and 12 months using a digital sphygmomanometer OMRON HEM-7114EF), with the appropriate cuff (adult or child). [39]. For children, the measures will be classified by age and height percentile. Adults’ measures will be classified according to international [40] and national [41] recommendations.

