**Fig. 1 Fig1:**
[figure not shown]
Flow Diagram

An effect size of 0.22 corresponds to a change of 5 min/day in moderate/vigorous PA (within-cell SD = 11) and a change of 5.4 min/day of sedentary time (within-cell SD = 12) [44].

Statistical analysis will be conducted on an intention-to-treat principle. Therefore, all children will be included in the analysis regardless of the intervention uptake. However, the percentage of “attendance” (compliance) of each child/family can be measured and will be used for subsequent analyses to evaluate the intervention uptake by the families.

Baseline characteristics will be described using summary measures and mixed models (with school as random effect), selected depending on their distribution. The effect of the two interventions on each one of the study outcomes will be estimated using a generalized mixed linear model with link and distribution selected according to the type of outcome. The model will include “active breaks” (AB), “virtual” (V), active breaks and virtual (AB + V), time (baseline/end of study) and the interactions time*AB, time*V and time*AB + V as fixed effect. It will also include random effects: child (or mother) to account for the repeated measures, and school to account for the cluster induced by the school. The most parsimonious model for each outcome will be reported. The False Discovery Rate criterion will be used to correct for multiple testing in non-planned analyses.

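### Child blood pressure and waist circumference are listed as outcomes only in classified form, which would cost power if they are modelled as listed

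*Protocol article*

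**What the plan says.** In the protocol article, Table 2 (Measures) separates the instrument from the outcome. For the child's anthropometry it records weight, height and waist, and the outcomes are "BMI Z-score, overweight, obesity and central obesity". Waist therefore appears only through central obesity, while BMI has both a continuous score and classes. For the child's blood pressure the instrument is a reading in mm Hg and the outcome is "Classification of blood pressure (high, normal or low").

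The section on anthropometric measures (Child and mother) agrees. Waist is taken finely: "Waist circumference will be measured to the nearest 0.1 cm at the end of gentle expiration". Central obesity in children is then defined by published cut-offs. Of blood pressure it says: "For children, the measures will be classified by age and height percentile". The anthropometric paragraphs close with: "Each measure will be repeated, and the average will be used for analysis".

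Statistical considerations then states: "The effect of the two interventions on each one of the study outcomes will be estimated using a generalized mixed linear model". Link and distribution follow the type of outcome. The model contains time and its interactions with the intervention components, plus random effects for child and school.

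The efficacy outcomes are listed just before Statistical considerations. The primary ones are minutes of moderate to vigorous activity and sedentary minutes. The secondary ones are four diet outcomes. Blood pressure and waist are in neither list.

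**The concern.** Two measures taken on a continuous scale at baseline and 12 months reach the outcome list only as a three-level class and a yes/no flag. If the model is fitted to them in that form, a change in waist or pressure that does not cross a cut counts as no change. The intervention contrast then rests on the children who cross a threshold. With 12 schools and about 160 children, some cells could be small: at an assumed 10% prevalence, 80 × 0.10 = 8 children on one side of a main effect would be above the cut. A null finding on these classes would then say little. The document gives no reason for treating these measures differently from BMI, whose Z-score is kept.

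**Working it through.** **Inputs from the document (Statistical considerations).** N = 160 analysed, 40 per arm, so 80 v 80 for a main effect; Cohen's f = 0.22; α = 0.05; stated power 80%. That calculation takes no account of clustering, and neither does this one, so only the outcome scale differs.

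**Assumptions.** The document gives no prevalence of central obesity or high blood pressure in these children, and no effect size for either measure. I use prevalences of 5% to 50%. The 21.6% in that range is the obesity prevalence that the Background quotes for an earlier study of 10–12 year olds, and serves only as a marker. The effect size is borrowed from the plan's activity outcomes. The underlying measure is taken as normal.

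**Step 1: the plan's figure.** Noncentrality λ = N f² = 160 × 0.22² = 7.744. With 1 and 156 degrees of freedom, power = 0.790. This agrees with the stated 80% to within about a point. For two equal groups, f = 0.22 is a difference of 2 × 0.22 = 0.44 SD.

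**Step 2: the same shift after a binary cut, at end of study.** With prevalence p above the cut, c = Φ⁻¹(1 − p). A shift of 0.44 SD towards lower values gives p₂ = 1 − Φ(c + 0.44). Power = Φ[(p − p₂ − 1.96·SE₀)/SE₁], where SE₀ is the pooled and SE₁ the unpooled standard error with 80 per side. Information retained for small effects = φ(c)²/[p(1 − p)].

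| p | c | p₂ | p − p₂ | SE₀ | SE₁ | Power | Information retained |
|---|---|---|---|---|---|---|---|
| 50% | 0.000 | 0.330 | 0.170 | 0.0779 | 0.0767 | 59% | 64% |
| 30% | 0.524 | 0.167 | 0.133 | 0.0669 | 0.0661 | 51% | 58% |
| 21.6% | 0.786 | 0.110 | 0.106 | 0.0584 | 0.0578 | 44% | 51% |
| 10% | 1.282 | 0.043 | 0.057 | 0.0407 | 0.0404 | 29% | 34% |
| 5% | 1.645 | 0.019 | 0.031 | 0.0288 | 0.0287 | 19% | 22% |

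For p = 50%: (0.170 − 1.96 × 0.0779)/0.0767 = 0.226, and Φ(0.226) = 0.589. Using SE₁ throughout moves each figure by about one point at most (44.9% at p = 21.6%).

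**Step 3: three ordered blood pressure levels.** With shares p_L below a and p_U above b, information retained = φ(a)²/p_L + [φ(a) − φ(b)]²/(1 − p_L − p_U) + φ(b)²/p_U. For low/high shares of 10%/10% this is 0.616, a loss of 38%. Other splits lose 35% (5%/20%), 47% (5%/10%), 58% (5%/5%), 60% (1%/10%) and 71% (1%/5%). A binary upper cut loses 66% at 10% and 78% at 5%, so an ordered model recovers part of the loss.

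**Step 4: change from baseline, which the model's time interactions address.** I simulated change scores with 80 per side and set the shift so that the continuous analysis has 80% power. Binary power at assumed within-child correlations of 0.5, 0.7 and 0.9 is about 47%, 39% and 26% at 50% prevalence; 30%, 26% and 18–19% at 21.6%; and 18%, 16% and 11% at 10%. The direction matches Step 2. The correlations are assumptions too.

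**The case against.** The strongest reply is that Table 2 is not the list of modelled outcomes. Its outcome column also holds socio-economic class and the home, neighbourhood and school environments. The home and neighbourhood questionnaire is given once, at 12 months, so no time interaction can be fitted to it. The column also omits outcomes that the article does analyse, such as number of snacks and sleep duration. Absence of waist in cm or pressure in mm Hg from the table therefore does not exclude a continuous analysis. The averaging sentence can be read as analysing mean waist in cm, and the flexible link would allow it. The body measure named in the specific aims is BMI, which stays continuous. An article that condenses a fuller protocol may leave the scale of such measures to that document.

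Much of this stands, and it is why the point is conditional. It does not remove the point. Table 2 calls the classes outcomes, the measurement section repeats the classification, and the model is said to cover each study outcome. The averaging sentence says how repeat readings are combined and may describe only the value that is then classified. It also comes before the blood pressure paragraph, so blood pressure has no continuous form anywhere in the text. BMI Z-score does not measure central fat.

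A reader might go further and infer that the effect model throws away most of the information in both measures, or that a null result would mainly reflect the cut. The document does not support that. In an end-of-study comparison a binary cut loses more than half only below about 21% prevalence, and several three-level splits lose less than half. The document gives no prevalence, within-child correlation or plausible effect for these measures.

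**Conclusion.** The point holds as a minor one. The article lists child blood pressure and waist as outcomes only in classified form, although the continuous values are collected. If the model is fitted to them as listed, power at the plan's own benchmark falls from about 79% to about 59% at best for a binary cut, and to about 19–45% at prevalences of 5% to 21.6%. An ordered three-level blood pressure class loses less. The loss appeared under every assumption tried, but its size depends on prevalences and an effect size that the document does not give, and clustering is ignored on both scales. Neither measure is a primary or secondary efficacy outcome, so the main conclusions and the sample size are unaffected. It would be wrong to read the text as ruling out an analysis of waist in cm.

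**What to change.** In Table 2 and in the section on anthropometric measures, add waist circumference (cm) and systolic and diastolic blood pressure (mm Hg, or age- and height-standardised values) as continuous child outcomes. Fit the model in Statistical considerations to them with a Gaussian distribution and identity link. Report central obesity and blood pressure class alongside as percentages by arm and time point.

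The cost is a wording change. It needs no new data, visits or participants. The small downside is a few more exploratory models (three continuous outcomes where two classified ones are listed now) and effects stated in cm or mm Hg, with the percentages there for readers who want the classes.

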#### Physical activity

The child’s PA and sedentary behaviour will be objectively assessed at baseline and 12 months with a tri-axial accelerometer (model GT3X+ ActiGraph, Pensacola, FL, USA). Accelerometer data will be collected and then downloaded in 15-s epochs. The accelerometer will be worn 24 h per day for 7 consecutive days (including the weekend days), placed on an elasticised belt at the waist on the right mid-axillary line. Mothers will be instructed on the placement and use of the accelerometer so as to guarantee correct compliance with the procedure. This will be done during the face to face interviews conducted at baseline and 12 months. They will be also instructed to remove the device when the child practiced water activities (bathe, swim or water sports). To guarantee correct compliance with the procedure in addition to receiving printed instructions, they will be contacted by the research team while the child is wearing the device in order to ensure proper use and to discuss any issue or doubt regarding information recording. The minimal acceptable amount of accelerometer data is 5 days including at least 1 weekend day; with at least10 hours of wear time per day. Periods of 60 or more minutes of continuous zeros will be considered no-use-times and will be excluded from analysis. After retrieval of the device, the research team will verify the data for completeness using the ActiLife 6.11.8 software (ActiGraph, Pensacola, FL, USA).

Accelerometer outcomes are: daily steps, minutes of PA, intensity of moderate to vigorous PA determined by Evenson et al.’s cut points and weekly METs during week days and during week-end days [28]. Evenson’s cut points define sedentary time that ranges from 0 to 100 counts per minute (cpm). In children of 5 to 8 years using ActiGraph accelerometers, the following classification is proposed: sedentary (0–100 cpm), light (101–2295 cpm), moderate (2296–4011 cpm), and vigorous (≥ 4012 cpm). These counts are based on 60-s epochs**.** Sedentary time and sleep duration will also be analysed. The ActiGraph accelerometers have the “inclinometer” function that determines the child’s position: sitting, standing, and lying down [29–31]. Sleep time is defined as the period elapsed from nocturnal sleep onset to nocturnal sleep offset, including all minutes scored as sleep or wake. Sleep period time for each child will be determined using a fully-automated algorithm specifically developed for use in the ISCOLE study and other epidemiological studies employing a 24-h waist-worn [29].

The mother’s PA and sedentary behaviour will be assessed with the Global Physical Activity Questionnaire (GPAQ), endorsed by WHO for surveillance of PA at a community level especially for developing countries (http://www.who.int/chp/steps/GPAQ/es/). It has acceptable validity and reliability; is able to adapt to take into account country’s cultural differences, and assesses information on sedentary behaviour and on PA at work, during leisure, and for transport [32, 33].

#### Dietary intake

Child’s and participant parent dietary intake and habits will be assessed at baseline and 12 months with a 24 h recalls using the Multiple Pass Method. This interview will be carried out at school, in a private space provided by the institution. A nutritionist will conduct the 60-min face to face interview with participating parent collecting the parent’s dietary intake and then the child’s [34]. A Visual Guide of Food’s Weight and Portions size will be used to help the parent identify the amount, portion size, weight, volume, size of the food item, and amount of liquid consumed the prior day [35]. ILSI Argentina contributed to the development of this support material and all the information obtained with this instrument will be analysed with the Nutrition Data System for Research software, version 2013 (NDS-R, Minnesota University, MN, USA) NDS-R software. Daily dietary intake outcomes are: daily caloric intake (Kcal/day), breakfast intake (yes/no), portions of fruits and vegetables, volume of water (units), and percentage of calories from total and saturated fats and of grams of added sugar coming from snacks.

### Anthropometric measures

#### Child and mother

Anthropometric measures will be taken at baseline and 12 months according to standardized procedures. Weight will be measured to the nearest 0.1 kg using a portable digital scale (SECA AURA 807) wearing light clothes. Height will be measured to the nearest 0.1 cm and with a portable stadiometer (SECA 206. Hamburg, Germany), with participant fully erect, without shoes, feet together, head in the Frankfort Plane and at the end of a deep inhalation. Waist circumference will be measured to the nearest 0.1 cm at the end of gentle expiration with a non-elastic anthropometric tape held midway between the lower rib margin and the iliac crest (Sanny, Berasil), utilizing the hands crossed technique in mid-waist for adults (WHO) and in minimal waist for children [36]. Central obesity in adults will be defined for each sex according to WHO recommendations [37] (females: > 88 cm; males: >102 cm). In children, central obesity will be defined using Taylor et al.’s cut-offs. [36]. The BMI Z-score will be calculated using the WHO reference growth charts for children [38] and for adults.

Each measure will be repeated, and the average will be used for analysis.

Blood pressure will be assessed at baseline and 12 months using a digital sphygmomanometer OMRON HEM-7114EF), with the appropriate cuff (adult or child). [39]. For children, the measures will be classified by age and height percentile. Adults’ measures will be classified according to international [40] and national [41] recommendations.

#### Environmental measures

Neighbourhood & home environmental characteristics will be assessed once, at 12 months post intervention with a modified and adapted version of the ISCOLE Neighbourhood & Home Environment Questionnaire administered to the mother [42]. It informs about the support given by the neighbours and family members as well as of the food and PA environment both of the home and neighbourhood. Social and economic status will be assessed with an adapted version of the SES Survey [43]. School environment will be assessed with a modified and adapted version of the ISCOLE School Environment Questionnaire [42]. This instrument will be administered to the headmaster, and assesses the school’s facilities, as well as the schools’ rules and current practices with regard to HE and PA.

One week after first evaluation, each participant parent will be e-mailed the first segment of the targeted content uploaded to the aforementioned multi-platform. The application was designed to register every visit so that the progress/hurdles regarding implementation of the proposed goals could be monitored on a one-to one basis. In order to enhance motivation and assess compliance, the content also inquired about the family’s habits and the children were able to interact with the platform via drawings and games (e.g. Memotest, etc). It is possible to view parental responses to the interactive questions, as well as the child’s drawings. If the parent failed to log in to the application within due time, she/he will be contacted via text message, or e-mail in order to be assisted in staying on track. The subsequent presentation will be forwarded 2 weeks after the presentation has been visited.

The efficacy of the intervention will be evaluated through outcomes measured on the children. Primary outcomes: (Aim 1 -PA): 1) Total time (minutes/day) of children’s moderate to vigorous PA and 2) Sedentary time (minutes/day). Secondary outcomes: (Aim 2 - Quality of diet): 1) Percentage of kilocalories (kcal) from added sugars, 2) Percentage of kcal from total fats and saturated fats, 3) Grams of fruits and vegetables, and 4) Number of snacks and kcal from total fats, saturated fats, and sugars coming from snacks. The 4 secondary outcomes will be measured by a 24-h recall, using the multiple pass method, applied to both mother and child and complemented with information regarding school breakfast and lunch in order to collect intake from an ordinary school day, covering both home and school.

### Statistical considerations

Sample size and power calculations. The number of children enrolled in first grade in the 12 participating schools is 405 [(range: 11–55, mean = 35]. Assuming approximately 50% participation rate the aim is to enrol a minimum of 200 dyads, i.e. 50 per trial arm. Assuming an additional 20% attrition it is expected to collect data on 160 dyads (40 per arm, an average of 13 per school) (Fig. 1). Under a factorial ANOVA design with two factors (V and AB interventions), and each at two levels, the target sample size of *N* = 160 participants (40 in each of the four conditions) yields a 80% power to detect an effect size of 0.22 (Cohen’s f low/moderate) for any of the main effects (V, AB) and the interaction effect (V*AB); F test, α = 0.05.

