### Study design

This is a cluster-randomized trial with four arms defined by a factorial structure of the two components of the intervention: the school-based (active breaks) (yes/no); family-based (web-based or virtual) (yes/no). The four arms of the study are: Active Breaks (AB) intervention, Virtual intervention (V), Active Breaks and Virtual intervention (AB + V) and neither AB nor V, control (C). The unit of randomisation is the school (rather than individual children/families). The study will run during two school semesters along two calendar years (the second semester of first grade and first semester of second grade). Because the enrolment process of families in the study lasted approximately 3 months, the study ran from July 2015 to November 2016.

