### Study population and randomization

The Ministry of Education of the city of Buenos Aires pre-selected a pool of public schools, which were invited to participate. Written invitations and an information pack were sent to each school Principal, followed up with visits to recruit schools. Consent was sought from Principals and first grade teachers. The 12 participating schools are located in middle-to low-income areas of the city. The schools were randomly allocated to one of the four intervention conditions using a computer generated random sequence. Blinding was not possible due to the characteristics of the intervention.

While part of the intervention is school-based, the primary outcomes are measured at subject level. Subjects of the study are first grade children. Mothers are also being assessed to evaluate parental factors; the dyad comprised the child and either parent or guardian in case the mother can’t attend the interview. All parents of first grade students (typically aged 6) of participating schools were invited to attend a meeting in which the nutritionist presented the program and described the study as well as the type of participation expected from parents and children. Those expressing interest were invited to enrol in the study and an initial face-to-face interview to be held at school was scheduled. Dyads were excluded if the child had severe intellectual difficulties or limitations to engage in physical activity, suffered from illnesses compromising nutrition or food selection, was taking medication known to affect body weight; or if the participating adult had severe intellectual difficulties. After screening for eligibility, the interviewer briefly explained the purpose and characteristics of the program and those who agreed to participate signed the informed consent form. Because the study is web-based, families without Internet access (at home, work or in the neighbourhood) are discouraged from participating. Should they still express wish to participate their data is collected but will be excluded from the analysis. Dyads attending a given school were assigned to the intervention condition randomly allocated to that school.

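### The 80% power figure treats 160 children as independently randomised, although only 12 schools are randomised; the design as calculated does not have the stated power

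*Protocol article*

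**What the plan says.** Under Study design, the article states: "The unit of randomisation is the school (rather than individual children/families". Study population and randomization adds: "The schools were randomly allocated to one of the four intervention conditions using a computer generated random sequence". There are 12 schools, and the same section notes: "While part of the intervention is school-based, the primary outcomes are measured at subject level".

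Statistical considerations then sets out the sample size: "it is expected to collect data on 160 dyads (40 per arm, an average of 13 per school". The power method follows: "Under a factorial ANOVA design with two factors (V and AB interventions), and each at two levels", applied to "160 participants (40 in each of the four conditions". The result is that this sample "yields a 80% power to detect an effect size of 0.22", claimed for both main effects and for the interaction, with an F test at α = 0.05. The effect is translated into 5 min/day of moderate to vigorous activity (within-cell SD 11) and 5.4 min/day of sedentary time (within-cell SD 12), the two primary outcomes.

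The analysis paragraph of the same section includes school as a random effect because children are clustered in schools. The power paragraph has no ICC, design effect, between-school variance or school-level degrees of freedom.

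**The concern.** The power calculation and the design use different units. Children in one school share teachers, playground, neighbourhood and the delivery of the intervention, so 160 children from 12 schools carry less information about a school-level factor than 160 children randomised singly. The number of schools also limits how well the error variance for that comparison can be estimated. The planned analysis recognises the clustering and the power statement does not.

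At stake is how the result will be read. The article claims 80% power for each component and for their interaction, and its Discussion expects to separate the value of each component. If true power is nearer one half, a null result says little, yet readers who trust the stated figure could take it as evidence that a component does not work.

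**Working it through.** **Inputs from the article (Statistical considerations):** N = 160; 12 schools; four conditions; f = 0.22; α = 0.05; SD 11 and 12 min/day; first-grade enrolment of 11 to 55 per school. Mean analysed cluster size is m = 160/12 = 13.33.

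**Assumptions:** ICC 0.01 to 0.10 (none is given); the quoted within-cell SD is the total SD between children in a condition.

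**Step 1: reproduce the stated figure.** For a one-degree-of-freedom effect in a 2×2 ANOVA, the noncentrality is λ = N·f² = 160 × 0.22² = 7.744, with 1 and 160 − 4 = 156 degrees of freedom. Power is 79.0%. From the minutes, f = 5/(2 × 11) = 0.227 gives 81.5% and f = 5.4/(2 × 12) = 0.225 gives 80.7%. The stated 80% is therefore the independent-children result and contains no hidden clustering allowance.

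**Step 2: allow for clustering.** The design effect is DE = 1 + (m − 1)·ICC = 1 + 12.33·ICC, and λ becomes 7.744/DE. The denominator degrees of freedom become 12 − 4 = 8, which raises the critical F from 3.90 to 5.32. The detectable f on 8 df is converted to a main effect by 2·f·SD.

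| ICC (assumed) | DE | Effective N | Power, 8 df | Power, 156 df kept | f for 80% power, 8 df | Activity, min/day (f × 22) | Sedentary, min/day (f × 24) |
|---|---|---|---|---|---|---|---|
| 0 | 1.00 | 160 | 68.5% | 79.0% | 0.253 | 5.6 | 6.1 |
| 0.01 | 1.12 | 142 | 63.5% | 74.2% | 0.268 | 5.9 | 6.4 |
| 0.02 | 1.25 | 128 | 59.0% | 69.7% | 0.283 | 6.2 | 6.8 |
| 0.05 | 1.62 | 99 | 48.6% | 58.5% | 0.322 | 7.1 | 7.7 |
| 0.10 | 2.23 | 72 | 37.5% | 45.7% | 0.378 | 8.3 | 9.1 |

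The 156 df column separates the two losses: the design effect alone already takes power below 80%, and the small number of schools takes it lower.

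**Step 3: unequal schools.** With coefficient of variation CV of cluster size, DE = 1 + ((1 + CV²)·m − 1)·ICC. With an assumed CV of 0.4, power on 8 df is 62.7%, 57.6%, 46.2% and 34.8% at ICC 0.01, 0.02, 0.05 and 0.10, a small further loss. With enrolment of 11 to 55 per school, allocating whole schools also cannot ensure the 40 children per condition that the calculation uses.

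**The case against.** The strongest reply is that the planned analysis is not a follow-up-only comparison. The model uses baseline and 12-month data with time-by-intervention terms, and the Abstract says the schools are matched. Both could recover precision. If baseline is credited as a (1 − r²) variance reduction, where r is the baseline to follow-up correlation, power on 8 df is:

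| r (assumed) | ICC 0.01 | ICC 0.02 | ICC 0.05 | ICC 0.10 |
|---|---|---|---|---|
| 0.5 | 75.7% | 71.3% | 60.2% | 47.3% |
| 0.6 | 81.9% | 77.9% | 67.0% | 53.4% |
| 0.7 | 89.4% | 86.2% | 76.6% | 62.9% |

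A high correlation with a very small ICC could therefore restore 80%. That much stands, and it means one cannot say that no analysis of these data could reach 80%.

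It does not rescue the statement as written, for three reasons. The power paragraph claims neither baseline adjustment nor matching. The planned time-by-intervention contrast compares changes, whose variance factor is 2(1 − r), not 1 − r². That gives no gain at r = 0.5. At r = 0.6 it gives 73.0% at ICC 0.01 and 57.5% at 0.05, and at r = 0.7 it gives 84.2% and 69.8%. And if the quoted SD already describes change, which the wording leaves open, no further credit is due.

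A second reply is that the model has only a school intercept, so stable school differences cancel from the time contrast. But schools can also differ in how their children change. The absence of a school-by-time term is a separate matter and does not make 12 schools equivalent to 160 independent children.

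It is also fair that equal allocation, three schools per condition, is inferred and not stated; the 8 df need only 12 schools in four conditions. And because the planned analysis includes school, this error does not by itself bias any estimate.

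**Conclusion.** The concern holds. The 80% figure is correct arithmetic for a design that is not this one. For the calculation as presented, any ICC of zero or more gives less than 80% on 8 df. Over the assumed range of 0.01 to 0.10, power is about 64% down to 38%, and the detectable main effect is 5.9 to 8.3 min/day of activity against the 5 stated. Someone who rejected the 8 df and kept 156 would still find 74% down to 46%.

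The size rests on the assumed ICC, on 13.3 analysed children per school and on the quoted SD being a total SD with no credit for baseline. Because the claim covers both primary outcomes and governs how a null result will be read, it should be corrected and not left to stand.

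**What to change.** Replace the power statement in Statistical considerations:

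- State an assumed ICC with a range and its source.
- Inflate the variance by 1 + (m − 1)·ICC, with the term for unequal school size.
- Use 8 denominator degrees of freedom.
- Report the power, or the difference detectable with 80% power, that 12 schools give: for example, about 7 min/day of activity at ICC 0.05 without credit for baseline.
- If credit for baseline measurement or matching is wanted, state the assumed correlation, say whether the SD is of level or of change, and derive the figure under the planned model.
- Drop the assumption of exactly 40 children per condition, or show the result under plausible imbalance.

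The cost is one rewritten paragraph and a less favourable power figure. No additional schools or children are asked for, and the trial's conduct does not change.
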